### Sample Size and Data Analysis

#### Sample Size

Data from a previous "feeding" trials including the DASH trial have estimated a standard deviation change in systolic blood pressure after the intervention was between 5.32 and 5.92 mmHg providing a 90% power [24]. In terms of change and blood glucose levels, 0.1 to 0.3 mmol. reduction are considered important in differentiation of the risk for the development of T2D [4]. For physiological outcomes' sample size estimate, we chose a mean difference between groups of 0.25 mm standard deviation as appropriate for change in vascular dimension. Previous work in our laboratory support the ability to detect the 2 mm difference in vessel diameter with a standard deviation of .025 mm following a similar lifestyle intervention. Hence, we required at least 10 subjects per group (two-tailed t-test, p < 0.025, power = 0.8). Assuming an 80% success rate in achieving suitable recordings in two test sites and a drop out rate of approximately 20%, we will recruit 40 subjects per treatment arm to the high normal blood pressure and IGT groups.

Initially, we anticipated recruiting about 5-10 patients per practice using a cluster design. To allow for the effect of this clustering we used an interpractice correlation coefficient (ICC) of 0.025. We felt this would be a conservative upper limit for the ICC on the basis of previous work in primary care. The inflation factor was therefore calculated to be 1+0.025 (10 minus 1) = 1.05. This figure gives a required number of patients per treatment arm of approximately 90 equivalent to 10 practices recruiting about 10 patients each.

However, there is some theoretical loss of power from using variable cluster sizes. This is negligible in the current study of approximately 50 patients per treatment arm. Hence, our allocation method of 10 patients per practice was designed to avoid this possibility. Statistical analysis will include differences among the subjects' characteristics in clinical, behaivoural, and physiological outcome measures using analysis of variance (ANOVA). Interactions and/or a specific age, gender, or clinical variable differences will be examined using Tukey's post hoc analyses. If a group difference in a potentially confounding variable is observed at limit differences in a key outcome, analysis of covariance (ANCOVA) will be performed with the potentially confounding variable serving as the covariant. Relations of interest will be initially identified by univariate correlation analysis. Independent correlations among the dependent variables will be determined using partial correlation analyses and/or conventional multivariate step-wise regression analysis. In all cases, probability levels will be p < 0.05.

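### The vascular sample size of 10 per group does not follow from the differences and standard deviations printed beside it

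*Protocol article*

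**What the plan says.** The vascular calculation is in the Sample Size section of the protocol article. The target is introduced as follows: "we chose a mean difference between groups of 0.25 mm standard deviation as appropriate for change in vascular dimension". The next sentence refers to the group's own experience: "Previous work in our laboratory support the ability to detect the 2 mm difference in vessel diameter with a standard deviation of .025 mm". The conclusion is drawn directly from these two sentences: "Hence, we required at least 10 subjects per group (two-tailed t-test, p < 0.025, power = 0.8").

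The 10 is then inflated for recordings that cannot be used, with success put at 80% in each of two sites, and for patients lost, put at about 20%. The recruitment figure that results is given in these words: "we will recruit 40 subjects per treatment arm to the high normal blood pressure and IGT groups". A later paragraph adds an allowance for clustering and arrives at about 90 patients per arm, described as 10 practices of about 10 patients.

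No other sample size is derived in the section. The blood pressure sentence gives a range for the SD of change and a power of 90%, but no target difference and no n. The glucose sentence gives only a range of change regarded as important.

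**The concern.** The two sentences give a difference of 0.25 (in mm or in SD units, since the phrase carries both), a difference of 2 mm, and an SD of 0.025 mm. That SD is a tenth of the 0.25 in the sentence before. Read as standardised differences, these values run from 0.25 to 80 SD. A sample of 10 per group at 80% power fits only a narrow band of effect sizes, so it can be checked whether any pairing falls inside it.

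Arterial flow-mediated dilation and function are among the primary outcomes, and the 10 per group is the only sample size in the section with a stated test, significance level and power. If it has no traceable basis, a reader cannot say what difference in vessel diameter a null result would exclude.

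**Working it through.** **Inputs, all from the Sample Size section.** Differences: 2 mm, 0.25 mm or 0.25 SD. SDs: 0.025 mm, or 0.25 mm if the fused phrase is read as an SD. Test: two-sample t-test, two-sided alpha 0.025, power 0.80, equal groups.

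**Formula.** With d = difference / SD, the normal approximation is n per group = 2(z₀.₉₈₇₅ + z₀.₈₀)² / d² = 2(2.241 + 0.842)² / d² = 19.01 / d². The last two columns use the t distribution (noncentral t, with simulation for the very large d).

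| Reading | d | n per group, normal | n per group, t | Power with 10 (t) |
|---|---|---|---|---|
| 2 mm, SD 0.025 mm | 80 | 1 | 2 | about 100% |
| 0.25 mm, SD 0.025 mm | 10 | 1 | 2 (simulated power 0.92) | about 100% |
| 2 mm, SD 0.25 mm | 8 | 1 | 3 | about 100% |
| 0.25 mm, SD 0.25 mm | 1 | 20 | 21 | 44% |
| 0.25 SD | 0.25 | 305 | 306 | 5% |

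The plan's figure of 10 is not reproduced by any row.

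**Working back from 10.** The normal approximation gives d = √(19.01 / 10) = 1.38; the t calculation gives 1.48. At an SD of 0.025 mm that is 1.48 × 0.025 = 0.037 mm. No such value is printed.

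**Other settings tried.**
- Two-sided alpha 0.05, the level in the analysis text: 1 SD needs 17, 0.25 SD needs 253, and 10 per group needs 1.32 SD.
- 2 mm as a slip for 0.2 mm, at alpha 0.025: 31 per group with SD 0.25 mm (d = 0.8), or 3 with SD 0.025 mm (d = 8).

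**From 10 to 40.** If 80% success applies at each of two sites and 20% drop out, 10 / (0.8 × 0.8 × 0.8) = 19.5, so 20; times two risk groups is 40. The 40 per arm can thus be reproduced from the 10.

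**What the planned numbers could detect (illustration).** Assumptions: ICC 0.025 as in the article; 10 practices per arm; a comparison on 18 practice degrees of freedom; alpha 0.025; 20% dropout; 80% usable recordings applied once. With m evaluable patients per practice, the design effect is 1 + 0.025(m − 1). The detectable d at 80% power is 3.319 × √(2 × design effect / n), where 3.319 is the noncentrality required with 18 df.

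| Recruited per arm | Evaluable n | m | Design effect | Detectable d |
|---|---|---|---|---|
| 40, both risk groups together | 40 × 0.64 = 25.6 | 2.56 | 1.039 | 0.95 SD |
| 40 in each risk group (80) | 80 × 0.64 = 51.2 | 5.12 | 1.103 | 0.69 SD |
| 100 (10 practices × 10) | 100 × 0.64 = 64 | 6.4 | 1.135 | 0.63 SD |

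**The case against.** **One reading does give 10.** A paired or one-sample t-test at 1 SD (0.25 mm over 0.25 mm) and two-sided 0.05 has power 0.803 with n = 10. This rules out saying that no reading whatever yields 10. But it needs a within-subject test where the text speaks of a difference between groups, an SD that is not clearly stated, and p < 0.025 read as the area in each tail. At two-sided 0.025 the paired n is 13.

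**A reader might infer that the trial is underpowered for the vascular outcome.** The document does not support that. It says "at least 10 subjects per group", and on the literal 2 mm and 0.025 mm that is far more than needed, with power of about 100%. Only if 0.25 SD was meant is the trial clearly too small: power before losses and clustering is 13% with 40 per arm and 31% with 100.

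**A reader might also infer that the whole recruitment target rests on the 10.** The 40 per arm does. The step to about 90 does not follow: the stated factor gives 40 × 1.05 = 42, and its own formula gives 1 + 0.025 × 9 = 1.225, hence 49. That is a separate problem.

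**Garbled units in a condensed article are a likely cause.** That may be so, but the point concerns figures that are printed, not detail left out. Within the stated between-group test, neither reading 2 mm as 0.2 mm nor moving between the two SDs recovers 10.

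**Conclusion.** The point stands as an error of derivation. With the stated test, the printed differences and SDs lead to 2 or 3, 21 or 306 per group, never to 10, which needs about 1.48 SD. The 10 and the 80% power attached to it are therefore unsupported as printed, and so is the basis of the 40 per arm. This conclusion needs no assumption beyond the two-sample test the article names.

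The direction of the error is not established, so no claim of inadequate or excessive power for vessel diameter should be made. The detectable differences of 0.95, 0.69 and 0.63 SD are illustrations. They depend on a practice-level test with 18 df that the article does not specify, on whether 40 per arm covers one risk group or both, and on counting the recording loss once. If usable recordings are needed at both sites, 40 per arm leaves 40 × 0.512 = 20.5 evaluable, and the detectable difference is larger.

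**What to change.** Replace the two input sentences with one between-group difference and one SD, both with units and both from the laboratory's own data, and name the test and alpha used. Recompute n and power from these and correct the stated 10 and 80%. Say whether 40 per arm is for both risk groups together or for each. Then state the difference that the planned sample can detect at 80% power after dropout, unusable recordings and clustering, on the same basis as the intended analysis.

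The direct cost is rewriting one paragraph and one short calculation. The downside is that the stated vascular sensitivity may become less favourable. Whether the number of patients should also change cannot be judged until the intended difference is stated.

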#### Secondary Outcome Measures

a) clinical - 24-hour ambulatory blood pressure; 2-hour glucose tolerance testing, hemoglobin A1C, microalbumin; waist circumference, calorie counts, b) behavioural measures - stage of change, self efficacy for diet and physical activity change, quality of life (SF36), barriers and benefits scales, c) physiological measures - waist circumference, calorie counts, dietary composition, cardiac function (echocardiographic determination of systolic and diastolic function, and left ventricular wall dimensions and volume), vascular geometry and elastic properties of the carotid and brachial arteries, muscle sympathetic and nerve activity discharge patterns at rest and a response to lower body negative pressure. Blood chemistry included blood lipid profiles homocystine, serum insulin, rennin, aldosterone, cortisol, C-reactive protein (CRP), markers of endothelial function including vascular adhesion molecule (VCAM) and intracellular cell adhesion molecule 1 (ICAM-1), urinary catecholamines, and serum free fatty acid composition.

Effects dependent on demographic subgroups will be defined by age, gender, and practice setting. Since previous trials have suggested that lifestyle interventions achieve their greatest effects early on, and that effects tended to diminish over time, we will evaluate the durability of these effects to 12 months and then for a further 12 months thereafter to determine the intervention rate of decay.

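### The base of 10 per group cannot be reproduced from any effect size the Sample Size section prints, and the 90% power for systolic blood pressure has no target difference

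*Protocol article*

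**What the plan says.** All of this is in the Sample Size section of the protocol article, unless another place is named.

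- **Vascular effect, first statement:** "we chose a mean difference between groups of 0.25 mm standard deviation as appropriate for change in vascular dimension".
- **Vascular effect, second statement:** earlier laboratory work is said to support the ability to "detect the 2 mm difference in vessel diameter with a standard deviation of .025 mm".
- **Base size:** "Hence, we required at least 10 subjects per group", with the conditions "two-tailed t-test, p < 0.025, power = 0.8".
- **Allowance for losses:** an 80% success rate for recordings at two test sites and about 20% dropout, after which "we will recruit 40 subjects per treatment arm to the high normal blood pressure and IGT groups".
- **Systolic blood pressure:** drawing on earlier feeding trials, the "standard deviation change in systolic blood pressure after the intervention was between 5.32 and 5.92 mmHg providing a 90% power". No difference, alpha or sample size goes with it. Clinic blood pressure is listed under Primary Outcome Measures.
- **Clustering:** an ICC of 0.025, leading to about 90 patients per arm, described as 10 practices with about 10 patients each.

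The data-analysis text that follows sets the significance level at 0.05 throughout, not the 0.025 used for sizing.

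**The concern.** The base of 10 is presented as the result of a calculation, and it is the only sample size derived from an effect, an alpha and a power. The two statements of the effect disagree with each other, and one of them (80 SD) is implausible as a planning value. If neither gives 10, the printed 80% power belongs to no effect in the document. The other power claim, for blood pressure, cannot be checked because power exists only in relation to a specified difference. A reader is then told that the trial has 80% and 90% power without being told what for.

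**Working it through.** **Inputs.** Two-sided alpha 0.025, power 0.80, equal groups. The vascular figures, losses, ICC, practice numbers and blood pressure SDs are all from the Sample Size section.

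**Step 1: try to reproduce 10 per group.** The normal formula is n = 2(z₁ + z₂)²/d², with z₁ = 2.241 (alpha 0.025, two-sided), z₂ = 0.842 (power 0.80) and d = difference/SD. The t column is the exact two-sample t calculation.

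| Reading | d | n per group, normal | n per group, t |
|---|---|---|---|
| 2 mm, SD 0.025 mm (as printed) | 80 | 1 | 2 |
| 0.25 mm difference, SD 0.025 mm | 10 | 1 | 2 |
| 2 mm difference, SD 0.25 mm | 8 | 1 | 3 |
| Difference of 0.25 SD | 0.25 | 305 | 306 |

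For the last row: 2 × (2.241 + 0.842)²/0.0625 = 304.2, rounded up to 305. Using 0.25 mm as both difference and SD (1 SD) gives 20 or 21. None gives 10.

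**Step 2: what 10 per group detects.** By the normal formula, d = (2.241 + 0.842) × √(2/10) = 1.38. By the t-test, d = 1.48. Neither value corresponds to an effect in the text.

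**Step 3: from 10 to 40.**

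- One 80% recording factor and 20% dropout: 10/(0.8 × 0.8) = 15.6.
- Both recording sites must succeed independently: 10/(0.8 × 0.8 × 0.8) = 19.5.
- Two risk groups, each rounded up to 16: 32.

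All three are below 40. The text also leaves open whether 40 is the total per arm or the number per arm in each risk group. The later figures do not settle it. With the section's own clustering formula, 1 + 0.025 × (10 − 1) = 1.225, 40 becomes 49 and 80 becomes 98. With the printed factor of 1.05 they become 42 and 84. The section gives about 90 per arm, and the next paragraph speaks of about 50.

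**Step 4: what the planned design detects for systolic blood pressure.** Take 10 practices per arm and 10 patients each, less 20% dropout, so 8 evaluable per practice and 80 per arm. The clustering factor is 1 + 0.025 × (8 − 1) = 1.175. The standard error of the difference is SD × √(2 × 1.175/80) = SD × 0.1714. With 20 practices there are 18 degrees of freedom, and the noncentrality needed for 90% power is 3.429 at two-sided 0.05 and 3.795 at 0.025.

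| Two-sided alpha | SD 5.32 mmHg | SD 5.92 mmHg |
|---|---|---|
| 0.05 | 3.429 × 0.1714 × 5.32 = 3.1 | 3.429 × 0.1714 × 5.92 = 3.5 |
| 0.025 | 3.795 × 0.1714 × 5.32 = 3.5 | 3.795 × 0.1714 × 5.92 = 3.9 |

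Entries are in mmHg.

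**The case against.** **A misprint.** The vascular figures may simply be misprinted. That is possible, but no correction is evident. A guess of 0.25 mm with SD 0.2 mm (1.25 SD), which is not in the text, needs 14 per group at the stated alpha and 12 at 0.05. A paired calculation for 1 SD at two-sided 0.05 does give 10, but the section specifies 0.025 and a size per group. It is also true that 10 satisfies a minimum of 2, but 10 is presented as following from the inputs, and it does not.

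**Blood pressure.** The 90% may describe the cited feeding trials rather than this one, and a condensed article can leave detail to the full protocol. The wording does not settle the first point. On the second, the objection is to a power figure that is printed and cannot be interpreted, not to missing detail.

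Four stronger conclusions might be inferred, and the document does not support them:

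- *The trial is some thirty times too small.* The 305 depends on reading the phrase as 0.25 SD, although a millimetre unit is printed in it. Other readings need only 2 or 3 per group.
- *The trial was sized on a secondary outcome.* The secondary list includes "vascular geometry and elastic properties of the carotid and brachial arteries", but flow-mediated dilation, a primary outcome, is itself a change in vessel diameter. The section does not say which of the two its vascular dimension means.
- *The 40 falls short.* It exceeds every figure that the stated losses produce.
- *A null result could not be interpreted.* It could still be read from the estimate and its confidence interval.

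**Conclusion.** The derivation is wrong as printed. At two-sided 0.025 and 80% power, the document's own inputs lead to 2 or 3 per group, or to about 305 if 0.25 SD is meant, never to 10. The step to 40 is unexplained but errs upward. The 90% power for systolic blood pressure has no difference attached.

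This is a failure of the stated justification. It does not show that the planned 10 practices per arm are too few. On the document's SDs, those practices give 90% power for 3.1 to 3.5 mmHg at two-sided 0.05, or 3.5 to 3.9 mmHg at 0.025. These figures assume 8 evaluable patients per practice, equal cluster sizes, an ICC of 0.025, and SDs from feeding trials that carry over to free-living patients. If the SD were 8 to 10 mmHg (an assumption, not in the document), the figure at 0.05 would be 4.7 to 5.9 mmHg. The document gives no blood pressure target against which to judge any of these.

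**What to change.** Rewrite the sample size paragraph:

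1. Give one vascular difference and one SD in consistent units, name the outcome they refer to, and recompute. If that cannot be done, delete the derivation of 10 per group.
2. State whether 40 is per arm or per arm within each risk group, and show the loss calculation that leads to it.
3. Use one alpha for sizing and analysis. The section now has 0.025 for the first and 0.05 for the second.
4. Replace the bare 90% with a statement such as: with 10 practices per arm, 8 evaluable patients each, ICC 0.025 and SD 5.32 to 5.92 mmHg, the trial has 90% power for a systolic difference of 3.1 to 3.5 mmHg at two-sided 0.05 (3.5 to 3.9 mmHg at 0.025). Label this a detectable difference, since it is worked back from the planned size and is not a target chosen for its clinical importance.

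The cost is one paragraph and no added patients. The trial's sensitivity becomes explicit and may look less favourable than the present wording suggests.

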**Methods/design:**

The Staged Nutrition and Activity Counseling (SNAC) study is a randomized clustered design clinical trial that will investigate the effectiveness and efficacy of a multi-component lifestyle intervention on cardiovascular disease risk factors and vascular function in patients at risk in primary care. Patients will be randomized by practice to either a standard of care lifestyle intervention or a behaviourally-based, matched prescriptive physical activity and diet change program. The primary goal is to increase physical activity and improve dietary intake according to Canada's Guides to Physical Activity Healthy Eating over 24 months. The primary intention to treat analysis will compare behavioral, physiological and metabolic outcomes at 6, 12 and 24 months post-randomization including estimation of incident hypertension and/or diabetes.

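### The primary analysis is labelled intention to treat and sizeable data loss is planned for, but the only named comparison, ANOVA/ANCOVA, in standard form uses only patients with the analysed value

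*Protocol article*

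**What the plan says.** The abstract of the protocol article (Methods/design) sets the label and the time points: "The primary intention to treat analysis will compare behavioral, physiological and metabolic outcomes at 6, 12 and 24 months post-randomization".

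The Sample Size section starts the vascular calculation from a small evaluable number: "Hence, we required at least 10 subjects per group (two-tailed t-test, p < 0.025, power = 0.8"). It then allows for two kinds of loss, "Assuming an 80% success rate in achieving suitable recordings in two test sites and a drop out rate of approximately 20" percent, and arrives at 40 recruits per treatment arm across the high-normal blood pressure and IGT groups. After a clustering allowance, the figure becomes about 90 per arm.

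Primary Outcome Measures lists clinic blood pressure, fasting glucose, fitness, BMI, and flow-mediated dilation of both the brachial and the carotid artery.

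The analysis text in the same section compares clinical, behavioural and "physiological outcome measures using analysis of variance (ANOVA"), with ANCOVA where a confounder differs between groups. No other method for the comparison between arms is named.

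Recruitment of Patients adds that patients whose blood pressure or glucose worsens during the randomization phase, so that other treatment is needed, are excluded and withdrawn. Their records are to be used to study prevalence and adherence.

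**The concern.** An intention-to-treat comparison should represent all patients in the arm to which their practice was allocated. A standard ANOVA or ANCOVA of an outcome at a given visit can include only those with a value at that visit. With 20% or more of values expected to be missing, the label and the named method fit poorly together.

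The plan answers expected loss only by recruiting more. That protects the number of evaluable patients, but those who remain may still differ between arms in ways related to the outcome. The named method also makes no use of earlier post-baseline values from patients who later leave, although the schedule collects them. Table 1, for example, has clinic blood pressure at weeks 8, 16, 24 and 52.

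At stake are whether the primary result describes all enrolled patients and, for flow-mediated dilation, how many contribute to it.

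**Working it through.** **Inputs (Sample Size section).** 10 evaluable per group; dropout about 20%, so 0.80 retained; recording success 80% in two test sites; target 40 per arm over two risk groups. The text does not say whether the 80% applies to each site or to both together.

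**Step 1: reproduce the 40 per arm.** Recruits per risk group = 10 / retained fraction, rounded up; then times 2 risk groups.
- 80% per site, both needed: retained 0.8 × 0.8 × 0.8 = 0.512; 10/0.512 = 19.5, so 20; × 2 = **40**, which matches.
- 80% for both sites jointly: retained 0.8 × 0.8 = 0.64; 10/0.64 = 15.6, so 16; × 2 = 32.
- Losses added (40%): 10/0.60 = 16.7, so 17; × 2 = 34.
- Dropout only: 10/0.80 = 12.5, so 13; × 2 = 26.

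Of these readings, only the first gives the plan's figure. The recruitment target is thus consistent with lost patients contributing nothing to the vascular comparison.

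**Step 2: share without a usable value on the plan's assumptions** (site failures and dropout taken as independent).

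| Outcome and reading | Missing | Left of 40 per arm | Left of 90 per arm |
|---|---|---|---|
| BP, glucose, fitness, BMI (dropout only) | 1 − 0.80 = 20% | 32 | 72 |
| Dilation, one usable site enough | 1 − 0.8 × (1 − 0.2²) = 23.2% | 30.7 | 69.1 |
| Dilation, 80% for both sites jointly | 1 − 0.64 = 36% | 25.6 | 57.6 |
| Dilation, 80% per site and both needed | 1 − 0.512 = 48.8% | 20.5 | 46.1 |

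**Step 3: what selection could do to the estimate.** This is an illustration by simulation. From the protocol comes the SD of systolic change, 5.6 mmHg (midpoint of 5.32 and 5.92), and 20% dropout. Assumed, because the documents give no figure: a true effect of 3 mmHg, a correlation of 0.5 to 0.7 between week-8 and final change, and informative dropout with log-odds rising by 1 per SD of poorer week-8 response. Estimated difference among patients with a final value:
- response-related dropout in SNAC only, random in control: 3.5 to 3.7 mmHg (overstated);
- the same mechanism within each arm: 3.0 (no bias);
- the same dependence on absolute response in both arms: about 2.8 (understated);
- response-related dropout in control only: 2.3 to 2.5 (understated).

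In the SNAC-only case, using the week-8 value recovers 3.0. Dropout was made to depend on that value alone, so the recovery is built in. It shows what a missing-at-random model can do, not that the assumption holds here.

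**The case against.** The strongest reply is that this is a condensed article. Rules for missing data usually sit in the full protocol or analysis plan, which are not shown, so their absence is no finding. The article never says that patients without a value are dropped, and ANOVA can be combined with imputation or take a repeated-measures form. Inflating recruitment is ordinary planning and does not define the analysis set. Some of the planned dropout may also precede baseline, since Recruitment of Patients foresees losses before baseline data collection and their replacement.

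Much of this stands. A reader might infer that the plan openly discards 20% to 49% of randomized patients on its primary outcomes. The documents do not support that: exclusion is an inference from the standard form of the method, the figures are planning assumptions, and 49% concerns only the vascular outcome on one reading.

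A reader might also infer that the result would be inflated by a given percentage. That needs a dropout mechanism confined to SNAC, which no text supports; other equally possible mechanisms give no bias or the opposite one. Nor is there ground for treating patients with a technically failed recording as having had no benefit. Recordings are made centrally by blinded assessors, and nothing suggests that failure depends on arm or response.

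What remains is not an objection to silence. The article states a label, an expected loss and a method that do not sit well together, and a better method is available from data already scheduled.

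**Conclusion.** The point holds as a worthwhile improvement to a stated method, not as proof of a biased result. On the plan's own assumptions, about 20% of patients would lack late values for blood pressure, glucose, fitness and BMI. For flow-mediated dilation the share is 23%, 36% or 49%; the last is the reading that reproduces 40 per arm. ANOVA/ANCOVA in standard form would leave these patients out, and larger recruitment does not correct for who they are. The size and direction of any bias cannot be derived from the documents.

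Separately, withdrawing patients whose blood pressure or glucose worsens sits uneasily with the intention-to-treat label, the more so because incident hypertension and diabetes are to be estimated. The article says that both arms face the same risk, but that need not hold if SNAC lowers blood pressure or glucose as intended. Timing of Recruitment places allocation of practices before patient recruitment, whereas Methodological Considerations & Limitations places recruitment before randomization. It is therefore unclear whether these withdrawals follow allocation. These passages must be reconciled.

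**What to change.** - **Primary comparison.** Replace ANOVA/ANCOVA with a likelihood-based repeated-measures mixed model with baseline value, arm, visit and arm-by-visit terms and a random effect for practice, which is the unit of randomization. Use all available post-baseline values of every enrolled patient, in the arm to which their practice was allocated.
- **Flow-mediated dilation.** Model brachial and carotid separately, so that a patient with one usable artery contributes. State whether the 80% success rate is per site or joint.
- **Follow-up.** Keep collecting the scheduled outcomes from patients who stop the programme.
- **Sensitivity analysis.** Add one for data not missing at random, for example setting missing SNAC values to the control-arm mean change.
- **Schedule.** Align Table 1 with Study Measurements. Table 1 ends at week 52 and marks fasting glucose at baseline only, while the text lists visits to 24 months. The model gains only where repeated values are actually collected.
- **Withdrawals.** Reconcile the withdrawal text in Recruitment of Patients with the intention-to-treat label, and say how these patients enter the comparison.

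The cost is revised wording, a little more programming and some follow-up effort. The model relies on data being missing at random, which the sensitivity analysis probes, and it cannot recover patients with no post-baseline value at all.

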### Study Population

Primary care practices will be recruited using a family practice research network. Randomization to intervention or usual care control will be done by a random number table. Recruitment of patients within the practices will include two successful strategies previously utilized by our group including opportunistic recruitment of consecutive patients during the course of routine, prescheduled, clinic visits or query of the network database for inclusion criteria and screening of patient visit lists [19,37]. All practices will target 10-12 patients each over a 6-month period.

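### The cluster inflation factor is given as 1.05, but the expression printed equals 1.225; the required number per arm cannot be reproduced from it, and the per-arm totals disagree

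*Protocol article*

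**What the plan says.** All but one of the statements are in the protocol article under Sample Size.

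- Base before clustering: after an allowance for unusable recordings and dropout, "we will recruit 40 subjects per treatment arm to the high normal blood pressure and IGT groups".
- Cluster size first expected: "Initially, we anticipated recruiting about 5-10 patients per practice using a cluster design".
- Correlation: "To allow for the effect of this clustering we used an interpractice correlation coefficient (ICC) of 0.025". The article calls this value a conservative upper limit.
- Factor: "The inflation factor was therefore calculated to be 1+0.025 (10 minus 1) = 1.05".
- Result: "This figure gives a required number of patients per treatment arm of approximately 90 equivalent to 10 practices recruiting about 10 patients each".
- The following paragraph, on variable cluster sizes: "This is negligible in the current study of approximately 50 patients per treatment arm".
- Under Study Population: "All practices will target 10-12 patients each over a 6-month period".

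Design and Recruitment of Practices both give 20 practices in total, which is 10 per arm.

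**The concern.** The opening of Methods/Design says that practices are randomized and patients are analysed. The inflation factor is the only numerical allowance for clustering in the article, and its printed value does not follow from the expression beside it. The number per arm is then said to follow from that value. A reader who relies on the text would believe that clustering costs 5% in sample size, when the stated correlation and cluster size make it 22.5%. The per-arm number also changes from about 90 to about 50 between adjacent paragraphs, so it is unclear which figure the calculation supports.

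**Working it through.** **Inputs.** Correlation 0.025 and cluster size 10 (Sample Size); 5-10 per practice as first expected (Sample Size); 10-12 per practice as the target (Study Population); 10 practices per arm (20 in total, Design and Recruitment of Practices); base of 40 per arm, or 40 in each of two risk groups (Sample Size).

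**1. The factor.** Inflation = 1 + ICC x (m - 1).

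| m per practice | ICC | Factor |
|---|---|---|
| 10 (as printed) | 0.025 | 1 + 0.025 x 9 = 1.225 |
| 5 | 0.025 | 1 + 0.025 x 4 = 1.10 |
| 12 | 0.025 | 1 + 0.025 x 11 = 1.275 |

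The printed 1.05 is not reproduced at any cluster size the article mentions. It would need m = 1 + 0.05/0.025 = 3 patients per practice, or an ICC of 0.05/9 = 0.0056 at m = 10.

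**2. The 90 per arm.** Using the article's own 1.05:

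- base 40: 40 x 1.05 = 42
- base 2 x 40 = 80: 80 x 1.05 = 84

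Neither is 90. If 90 did come from multiplying by 1.05, the base was 90/1.05 = 85.7, a number that appears nowhere in the text. The article also equates about 90 with 10 practices of about 10, which is 100.

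**3. The requirement with the right factor.**

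| Base per arm | x 1.05 | x 1.225 | Is 90 enough? | Is 10 x 10 = 100 enough? |
|---|---|---|---|---|
| 40 (40 is the whole arm) | 42 | 49 | yes | yes |
| 80 (40 in each risk group) | 84 | 98 | no | yes |
| 85.7 (backed out of 90) | 90 | 105 | no | no, short by 5 |

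The largest base that 100 per arm covers is 100/1.225 = 81.6. At 12 per practice the recruited number is 120 and the factor 1.275, which covers a base up to 120/1.275 = 94.1.

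**4. The totals.** The clustering paragraph gives about 90, equated with 100. The paragraph after it gives about 50 and also refers to 10 patients per practice. With 10 practices per arm, 10 per practice is 100, not 50. The 50 is close to 40 x 1.225 = 49 and also equals 10 practices x 5 patients; the article does not say which, if either, was meant.

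**The case against.** The arithmetic slip itself has no good defence. A misprinted correlation is conceivable, since 0.005 gives 1 + 0.005 x 9 = 1.045, but 0.025 is printed twice and described as a conservative upper limit. The objections that carry weight concern the consequences.

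- **The requirement is not shown to be too low.** This stands as a limit. If 40 is the whole arm, the corrected need is 49 and 90 exceeds it.
- **Recruitment may already be adequate.** The working quota is steady at about 10 per practice in 20 practices, so about 100 per arm. That covers a base of 40 or 80. It softens the practical effect but corrects neither the printed factor nor the 90.
- **Some of the differing numbers are not contradictions.** This is right. The 40 comes before the clustering step, the 5-10 is introduced as an initial expectation, and a target of 10-12 is compatible with needing about 10. The real conflict is 50 against 90 and 100.

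A reader might infer that the trial is underpowered by a definite amount, for example by taking 80 per arm as the number that just gives 80% power. The article does not support that. It attaches 80% power to 10 subjects per group (two-tailed, 0.025) for a vascular outcome, and reaches 40 only after mentioning unusable recordings and dropout. Counting those allowances as power requirements would be an error: 40 x 0.8 x 0.8 = 25.6 evaluable, and 25.6/1.225 = 20.9 effective, still above 10. Nor does this show that power is adequate. The step from 10 to 40 is itself not explained by the stated rates (10/0.64 = 15.6), and the 10 covers only one outcome. Power simply cannot be recomputed from this text.

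**Conclusion.** The factor is wrong as printed: 1.225, not 1.05, so the inflation is 22.5% instead of 5%. This needs no assumption beyond the article's own correlation and cluster size. It is also certain that 90 does not reproduce from a base of 40 or 80, and that about 50 per arm conflicts with about 90 and with 10 x 10 = 100.

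Whether the requirement is understated depends on a base that the article leaves ambiguous. The corrected figure is 49, 98 or 105 per arm for a base of 40, 80 or 85.7, so 90 is sufficient on the first reading and too low on the other two. For the same reason, neither a single replacement number nor the claim that no further patients are needed follows from the text. The point should still be corrected, because the stated allowance for clustering is false on its own inputs and the required number is said to rest on it.

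**What to change.** 1. Replace 1.05 with 1.225, or with 1.275 if 12 patients per practice is the planning size.
2. State the number per arm before clustering, and say whether 40 is the whole arm or applies to each risk group.
3. Recompute the required number per arm from that base and show the multiplication.
4. Give one per-arm total throughout and reconcile the 50, 90 and 100. If the 50 is a per-risk-group figure, label it so; otherwise correct or remove it.
5. If the base proves to be 85.7, 100 per arm falls 5 short of 105. In that case restate the power or the requirement.

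For a base of 40 or 80 this is a correction of text, with no change to the planned 10 practices x 10 patients per arm. The cost is that the stated margin becomes less favourable: any requirement built with 1.05 rises by 1.225/1.05, about 17%.
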